**Methods/design:**

This multicentre, open-label, randomized controlled trial will be conducted in 300 patients with COVID-19. The patients will be randomly (1:1) divided into a treatment group and a control group. All patients will receive standard therapy at the same time. Patients in the experimental group will receive Baidu Jieduan granule treatment twice a day for 14 days. The outcomes will be assessed at baseline and at 3, 5, 7 and 14 days after treatment initiation. The primary outcome will be the rate of symptom (fever, fatigue and coughing) recovery. Adverse events (AEs) will be monitored throughout the trial.

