## Introduction

An outbreak of coronavirus disease-2019 (COVID-19) in Wuhan city, China, has resulted in a global health emergency, with over 61.8 million confirmed cases, including over 1.4 million deaths as of 29 November 2020 around the world [1]. The number of patients may be underestimated due to asymptomatic individuals or individuals with moderate symptoms [2]. At present, scientists are sure that COVID-19 is caused by a new virus, named “severe acute respiratory syndrome coronavirus 2 (SARS-CoV-2)” [3]. Patients suffer from fever, fatigue and dry cough, with some progressing to breathing difficulties, acute respiratory distress syndrome or sepsis [4]. The disease is diagnosed by clinical characteristics, epidemiological history and laboratory test results according to the “Guidelines for the Diagnosis and Treatment of Novel Coronavirus (COVID-19) Infection by the National Health Commission (Trial Version 7)” [5].

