### Patient withdrawal

Enrolment without meeting the inclusion criterionUnsuitability for the trial due to deterioration or recovery of the patient’s conditionPoor patient complianceVoluntary withdrawal

Upon patient withdrawal from the trial, all collected data up to the time of withdrawal will remain in the database. Safety-related information may be obtained until the 14th day after withdrawal if possible.

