### Outcomes and measurements

The primary outcome will be the proportion of negative SARS-CoV-2 nucleic acid results on the 14th day. The secondary outcomes will be the time to symptom recovery, the proportion of cases with reversion on chest CT, the time to negative SARS-CoV-2 nucleic acid results and the proportion of participants regrouped as severe cases. Symptom recovery is defined as the complete disappearance of fever, fatigue and coughing symptoms.

Evaluation of the primary and secondary outcomes will occur at five points (before treatment and the 3rd, 5th, 7th and 14th days of hospitalization).

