### Statistical analysis

We will not conduct subgroup or adjusted analyses of the trial. The independent statistical analysts will be responsible for the data analysis. All patients will be analysed on the basis of intent-to-treat analysis, including all randomized subjects who take Baidu Jieduan granules at least once and have follow-up information recorded. In the case of missing data, multiple imputation will be carried out to generate missing values. A per-protocol analysis, which includes patients who completed the trial without conflict with the major protocol, can be conducted as appropriate. Then, the statistician will submit statistical reports in a timely manner to the study director. The statistical analysis will be performed in a blinded manner using SPSS 20.0 software. Continuous variables characterizing each study group will be expressed as the mean with standard deviation or median with interquartile range. Categorical variables will be reported as frequencies and proportions. Continuous outcomes will be analysed by unpaired Student’s *t*-test or Wilcoxon’s nonparametric statistic, while count data will be compared using a chi-square test or Fisher’s exact test. All statistical tests will be two-sided. *P* < 0.05 will be considered statistically significant. We will not carry out an interim analysis.

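### The only missing-data rule is multiple imputation, with no exception for death and no outcome that scores it, so a patient who dies before day 14 may be given an imputed success

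*Protocol article*

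**What the plan says.** Four statements in the protocol article bear on this.

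- **Missing data** (Statistical analysis): "In the case of missing data, multiple imputation will be carried out to generate missing values". No kind of missingness is exempted.
- **Outcomes** (Outcomes and measurements): "The primary outcome will be the proportion of negative SARS-CoV-2 nucleic acid results on the 14th day". The secondary outcomes are two times (to symptom recovery and to a negative test), CT reversion, and "the proportion of participants regrouped as severe cases". The definition of recovery reads: "Symptom recovery is defined as the complete disappearance of fever, fatigue and coughing symptoms". None of these names death or requires the patient to be alive. The Abstract gives a different primary outcome, "The primary outcome will be the rate of symptom (fever, fatigue and coughing) recovery", which does not mention death either.
- **Analysis set** (Statistical analysis): labelled intent-to-treat, but defined as "including all randomized subjects who take Baidu Jieduan granules at least once and have follow-up information recorded".
- **Withdrawal** (Patient withdrawal): deterioration is a listed ground. For a withdrawn patient, "all collected data up to the time of withdrawal will remain in the database"; after that, only safety information may be sought, if possible.

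**The concern.** A patient who is alive but was not swabbed on day 14 has a value that was not observed, and imputation is a reasonable way to deal with it. A patient who died on day 9 has no day-14 value at all. The stated rule treats the two alike and generates a result for both. The worst clinical outcome can then enter the primary analysis as a success.

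If one arm has more deaths, that arm also has more generated results, and the primary comparison loses some or all of the difference. The trial enrols adults up to 85 years, its inclusion criteria set no severity limit, and it expects some patients to become severe, so deaths cannot be ruled out.

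**Working it through.** **Step 1. What happens to a death under the stated rules.** The article gives no figure for deaths, so there is no planned value to reproduce. The rules can be followed case by case. I read the dose condition as the start of allocated treatment in either arm; read literally, control patients could not meet it, which is a separate matter.

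| Patient | In the analysis set? | Day-14 value |
|---|---|---|
| Dies after a dose and at least one recorded follow-up | Yes | Imputed; may be negative or recovered |
| Dies before any follow-up is recorded | No | None; drops out of the analysis |
| Withdrawn for deterioration after some follow-up, then dies | Yes | Imputed; efficacy data stop at withdrawal |

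The safety sections do not fill the gap. Adverse event reporting defines an event by its connection with the granules. A death from COVID-19, or any death in the control arm, falls outside that wording. Safety outcomes lists vital signs, laboratory tests and ECG, not mortality.

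**Step 2. Size of the effect.**

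Inputs:
- N = 150 per arm (Sample size), taken as all in the analysis set.
- D = deaths in an arm. Assumption: the article gives no trial mortality.
- p = proportion negative among survivors. It cancels below.
- q = chance that a dead patient is imputed negative. Assumption: 0.50 to 0.85, because the imputation model is not described.

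Proportion negative in one arm:
- deaths imputed: [p(N − D) + qD] / N
- deaths counted as not negative: p(N − D) / N
- difference between the two: qD / N

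The shift in the arm difference is therefore q × (excess deaths in one arm) / N.

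| Excess deaths | q = 0.50 | q = 0.85 |
|---|---|---|
| 3 (for example 5 v 2) | 1.5/150 = 1.0 points | 2.55/150 = 1.7 points |
| 5 (6 v 1) | 2.5/150 = 1.7 points | 4.25/150 = 2.8 points |
| 7 (7 v 0) | 3.5/150 = 2.3 points | 5.95/150 = 4.0 points |

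**Step 3. What is hidden.** Suppose mortality is 5% v 1%, survivors are negative equally often in both arms, and the dead are imputed at the survivors' rate (all assumptions). The imputed analysis shows a difference of 0. Counting deaths as not negative gives 0.80 × (5 − 1) = 3.2 points, or 0.90 × (5 − 1) = 3.6 points, against the arm with more deaths.

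**Step 4. Scale.** With 150 per arm and a two-sided 5% test, 80% power corresponds to about 85% v 94.7% (9.7 points) or 61.1% v 76.1% (15.0 points). The planning difference for symptom recovery is 91.2 − 61.1 = 30.1 points. A shift of 1 to 4 points is small beside any of these.

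**The case against.** The strongest objection is that the article never says a death is coded as missing. A condensed article may leave the scoring of deaths to a full protocol or analysis plan that is not shown. This stands as a limit: the consequence is inferred from a rule without exception and the absence of any other rule. But the point is more than missing detail. The article fixes a general rule which, applied as written, generates values that cannot exist, and an analysis plan would have to depart from it to avoid that.

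Several stronger readings are tempting and are not supported.

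- *Every death before day 14 is imputed.* The analysis-set definition drops patients without recorded follow-up, so the earliest deaths are excluded. That is a different error.
- *Most of the dead would score as successes.* The imputation model is unspecified. One that used the day 3, 5 and 7 assessments could give a deteriorating, swab-positive patient a low chance of being negative. Hence the 50% lower value; the true chance could be lower still.
- *A mortality effect would show in no outcome.* A patient who dies of COVID-19 in hospital would often be classed as severe first, so the progression outcome would catch some deaths. It does not change the primary scoring.
- *The trial should expect about 2.3% mortality.* The Introduction speaks of a pandemic "with over 61.8 million confirmed cases, including over 1.4 million deaths as of 29 November 2020 around the world", and 1.4/61.8 = 2.3%. That is a crude worldwide ratio across all severities. The title concerns moderate disease, so deaths may be few.

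Two further points are fair. Some deaths will follow withdrawal for deterioration, so this overlaps with the handling of withdrawals. And scoring death as failure is one defensible strategy among several. Neither justifies imputing a value for a patient who has died.

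**Conclusion.** The point holds in a limited form. The stated rule imputes day-14 results for patients in the analysis set who have died and omits those who die before any follow-up, and no outcome scores death. The shift in the arm difference is about 1 to 4 percentage points, assuming 3 to 7 excess deaths in one arm of 150 and a 50% to 85% chance of being imputed negative. With fewer or evenly divided deaths it is smaller, possibly nil.

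This alone is unlikely to reverse the trial's conclusion. It should still be corrected, because it can hide or dilute a mortality difference in the primary result, and because in an open-label trial the scoring of deaths should not be chosen after they have occurred.

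**What to change.** In Outcomes and measurements and in Statistical analysis:

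1. State that any randomized patient who dies before day 14, including one with no recorded follow-up, is kept in the analysis and counted as not negative and not recovered on the binary outcomes.
2. Restrict multiple imputation to patients known to be alive on day 14.
3. Report deaths by arm, whatever their judged relation to the granules.

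A reasonable addition is to count death in the progression outcome, so that it covers patients who became severe or died by day 14. This changes a secondary endpoint and should be labelled as such.

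The cost is a few sentences, filed as an addendum for ethics re-review as the Ethics section requires, and best settled before data lock. The success rate falls slightly in any arm with deaths. Vital status at day 14 must be confirmed for discharged or withdrawn patients. The telephone contact after discharge (Quality control) and the safety follow-up after withdrawal (Patient withdrawal) offer a route, although the latter is promised only where possible.

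### Time to symptom recovery and time to negative PCR fall by default under t or Wilcoxon tests with no rule for patients without the event by day 14, and the visit days are counted from two different origins.

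*Protocol article*

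**What the plan says.** Two secondary outcomes in Outcomes and measurements are times. The list begins "The secondary outcomes will be the time to symptom recovery, the proportion of cases with reversion on chest CT" and continues with "the time to negative SARS-CoV-2 nucleic acid results and the proportion of participants regrouped as severe cases". The event for the first is strict: "Symptom recovery is defined as the complete disappearance of fever, fatigue and coughing symptoms". The other efficacy outcomes, including the day-14 PCR primary, are proportions.

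Statistical analysis names two pairs of tests. "Continuous outcomes will be analysed by unpaired Student" t-test or Wilcoxon's test, while "count data will be compared using a chi-square test or Fisher" exact test. Multiple imputation is the only provision for absent values. The article mentions no survival method, no censoring rule and no value for a patient without the event.

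The visit days are stated twice. Outcomes and measurements places evaluation of primary and secondary outcomes at five points: "before treatment and the 3rd, 5th, 7th and 14th days of hospitalization". The abstract (Methods/design) says: "The outcomes will be assessed at baseline and at 3, 5, 7 and 14 days after treatment initiation". Nothing in the article reconciles the two.

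**The concern.** A t-test or Wilcoxon test needs a number for every patient. A patient still symptomatic or PCR-positive at day 14 has no event time, only the knowledge that it exceeds 14 days. The text leaves the analyst three options, none of them specified: drop such patients, assign them a value, or treat the time as missing and impute it. Dropping them compares only patients selected on the outcome. Imputing creates times for events that did not occur in the window. The results can differ widely, and in an open-label trial that choice should not be left open.

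The time origin is a matter of definition. The two outcomes have no origin of their own and inherit that of the visits. If hospital days and days since treatment start do not coincide, the recorded times and the day-14 primary measure different things depending on which section a centre follows.

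**Working it through.** **Which test applies.** The two times are the only efficacy outcomes that are not proportions, so among efficacy outcomes the rule for continuous data can apply only to them. The protocol has no computed figure for these outcomes to reproduce.

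**Share without the event.** Sample size gives recovery rates of 91.2% (TCM) and 61.1% (conventional) from a similar trial, with no time horizon. Assume they hold at day 14:
- granules: 1 − 0.912 = 8.8%, or 150 × 0.088 ≈ 13 patients;
- control: 1 − 0.611 = 38.9%, or 150 × 0.389 ≈ 58 patients;
- overall: (13.2 + 58.35)/300 = 23.9%.

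For PCR there is no rate. A day-14 proportion as primary outcome implies only that some patients are expected not to be negative. At an assumed 5%, 20% or 40% not negative, 15, 60 or 120 of 300 patients have no time.

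**Effect of using recoverers only.** Assume exponential times matched to those rates, λ = −ln(1 − p)/14.
- λ = 2.430/14 = 0.1736 and 0.944/14 = 0.0674; hazard ratio 0.1736/0.0674 ≈ 2.6.
- Medians ln 2/λ: 3.99 and 10.28 days, a difference of 6.3.
- Mean among those with an event by day 14, 1/λ − 14(1 − p)/p: 5.76 − 1.35 = 4.41 and 14.83 − 8.91 = 5.91, a difference of 1.5.
- As a comparison of means that keeps everyone, mean event-free time to day 14 is p/λ: 0.912 × 5.76 = 5.25 and 0.611 × 14.83 = 9.06, a difference of 3.8.

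**Power.** Simulation with 135 evaluable patients per arm (150 less 10%), exponential times, control at 61.1% by day 14, events recorded at the next visit (3, 5, 7 or 14), two-sided 0.05. Ranges show separate runs; the hazard ratios 1.4 and 1.6 are assumptions.

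| Analysis | HR 1.4 | HR 1.6 | Planning rates (HR ≈ 2.6) |
|---|---|---|---|
| t-test, recoverers only | 10–11% | 17% | 74–75% |
| Wilcoxon, non-events set to 14 | 41–44% | 71–72% | about 100% |
| Wilcoxon, non-events ranked last | 58–59% | 86% | about 100% |
| Log-rank | 62–63% | 88–89% | about 100% |

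With no effect, rejection was about 5% for each method checked. At an assumed 75% versus 61.1% by day 14, recoverers-only t and Wilcoxon each reach 12%, Wilcoxon with non-events last 71%, and log-rank 74%. If the arms differ at 91.2% versus 61.1% in the share recovering, but not in speed among recoverers, the recoverers-only tests reject in about 5% of trials and log-rank in about 100%.

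**Clock.** The inclusion criteria set no limit on time since admission. For illustration, if randomization and treatment start fall on hospital day 5, hospital day 14 comes 14 − 5 = 9 days later, and hospital day 3 precedes treatment. If treatment starts on the day of admission, the two clocks agree, apart from whether that day is counted as 0 or 1.

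**The case against.** The strongest reply is that Statistical analysis never names the two times. It speaks of continuous outcomes, the safety laboratory values fit that description, and a survival method may stand in an unseen analysis plan. It is true that the assignment is by default. But no other efficacy outcome fits the sentence, and the imputation rule is written without exception, so a plan naming log-rank would have to depart from the published text.

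Second, Wilcoxon is a named test and performs nearly as well as log-rank when non-events are ranked last. This stands. A reader might infer that Wilcoxon itself costs the power; it does not. The loss comes from dropping non-events or tying them with day-14 recoverers, and at the planning effect every method that keeps them has ample power. But ranking them last is not specified, and it needs follow-up to day 14. Patient withdrawal allows exit when a patient's condition worsens or resolves.

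Third, some stronger readings are not supported:
- That 38.9% of controls will not recover in the window: the source rates carry no horizon.
- That many patients will lack a PCR event: no rate is given.
- That hospital days start before randomization: the article does not date one against the other.
- That controls have no treatment start: the abstract gives standard therapy to all patients.

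The clock conflict is thus a contradiction to reconcile, not a demonstrated distortion.

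**Conclusion.** The point holds in two parts. As written, the protocol gives the two time-to-event outcomes tests that have no defined input for patients without the event, and an imputation rule that could supply one improperly. The size depends on how non-events are handled: negligible if all are kept and ranked last with complete follow-up, severe if they are dropped (about 10% against about 62% power at an assumed hazard ratio of 1.4, and a 6.3-day difference in medians appearing as a 1.5-day difference in means among recoverers). These figures rest on exponential times and on reading the planning rates as day-14 rates.

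The two visit clocks contradict each other and diverge whenever randomization does not fall on the day of admission. Because the PCR primary in Outcomes and measurements is read on day 14, this part reaches the primary outcome; the test choice concerns secondary outcomes only. The change should be made before analysis.

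**What to change.** - Reconcile the abstract and Outcomes and measurements to one origin common to both arms, randomization, for all outcome assessments, including the day-14 primary.
- Analyse both times with Kaplan-Meier curves and a log-rank test, or with a discrete-time or interval-censored model matching the visit days.
- Censor event-free patients at day 14 or at their last assessment. Keep deaths and withdrawals for deterioration in the risk set to day 14 as non-events, since plain censoring there would be informative. Count withdrawals for recovery by their recorded status on each outcome.
- Do not impute event times for patients known to be event-free at day 14.

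Stratifying the test by centre is optional; Statistical analysis currently excludes adjusted analyses.

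The cost is a few sentences in the protocol and analysis plan, standard procedures for Kaplan-Meier and log-rank, and visit days counted from the randomization date. The sample size does not change.

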### Trial oversight

#### Coordination Centre

The membership of the Coordination Centre will consist of clinical experts, statisticians and quality control experts from each centre. The centre will be responsible for the management of the clinical research trial, cooperative hospitals and preclinical trial training courses and resolving key issues in the whole process of study.

#### Quality control

All centres and researchers will be regularly monitored and supervised by a clinical research organization (CRO) throughout the trial, according to the standard protocol.

### Data management

Trained research staff will collect trial data carefully according to a standard protocol and will complete paper case report forms (CRFs) accurately, completely, timely and reliably. The data will be entered into the electronic data capture (EDC) system and regularly reviewed by a clinical research associate (CRA). If any changes are implemented by researchers, feedback will be provided to the researchers and CRA. All modifications and paper CRF transfers between investigators, inspectors and data managers will be documented and maintained appropriately. The data administrators will lock the data on completion of the study. The medical information of all the study participants will be kept strictly confidential. The SPIRIT flowchart of the study is shown in Fig. 2. Research findings will be announced via publication and conferences, both nationally and internationally. After the study is published, the data will be made available in an appropriate manner.

**Fig. 2 Fig2:**
[figure not shown]
Study procedures and assessments. CT computed tomography, SARS-CoV-2 severe acute respiratory syndrome coronavirus 2

### Quality control

All investigators of the trial will be trained strictly and comprehensively by the State Food and Drug Administration, following Good Clinical Practice (GCP), to thoroughly comprehend the procedure of the trial and improve compliance. All qualified researchers will collect data and complete the CRF in an accurate and complete manner. After discharge, the subjects will be followed up by phone. Regular monitoring and inspections will be conducted by the CRO once a month to confirm the reliability of the related research data and the trial process. The CRO will check details on informed consent, the inclusion and exclusion criteria, the original data, the management of AEs, the process of storage and distribution of the research drugs and the CRF.

### Ethics

This trial will comply with the principles of the Declaration of Helsinki and the regulations on the quality management of clinical trials in China. The research protocol has been approved by the Ethics Committee of Huangshi Hospital of Traditional Chinese Medicine (approval number HSZY-PJ-2020-002-01) and registered with the Chinese Clinical Trial Registry (ChiCTR2000029869). Any changes to the trial protocol will be maintained as a program addendum, and the revised protocol will be submitted to the Ethics Committee for rereview. The trained principal investigators or study coordinators will recruit the patients and conduct the process of obtaining informed consent. They will need to ensure that study participants or legal representatives receive sufficient information and time to sign the informed consent form prior to the study. Any modification of the study protocol or AEs attributable to this study will be reported to the research ethics committees.

